2. appearance of any *P. vivax* parasitaemia within 42 days after treatment for vivax malaria.

Secondary endpoints in falciparum malaria will be:

1. reappearance of PCR-uncorrected *P. falciparum* parasitemia,
2. appearance of any *P. vivax* parasitemia, and
3. appearance of *P. falciparum* gametocytes, all within 42 days.

Secondary endpoints in vivax malaria will be:

1. reappearance of any *P. vivax* parasitemia within 28 days, and
2. appearance of *P. vivax* gametocytes within 42 days.

Other secondary endpoints for each *Plasmodium* species will be initial fever and parasite clearance times (the times to the first of two consecutive assessments at which the child was afebrile and slide-negative, respectively), and drug safety including haemoglobin levels.

*Sample sizes:* Sample size calculations21 for the present trial are based on the assumptions that i) the *P. falciparum* Day 42 PCR-corrected ACPR for AL is 95.2%8 with a non-inferiority margin of 5% for AP and AN, ii) the *P. vivax* Day 42 uncorrected ACPR for AP and AN is at least double the 30.3% found previously for AL (as for DP in the original trial8), iii) there will be equal numbers in each treatment arm, and iv) there will be a 25% attrition rate:

| Study | Type | Total *n* | *n*/group with drop-outs | Power | Α |
| --- | --- | --- | --- | --- | --- |
| *P. falciparum* | Non-inferiority | 515 | 220 | >80% | 0.05 (one-tailed) |
| *P. vivax* | Superiority | 122 | 60 | >90% | 0.05 (two-tailed) |

*Subjects:* Children aged 0.5-5 years with an axillary temperature >37.5°C or fever during the previous 24 hours will be screened using on-site blood film microscopy. Those with either *P. falciparum* (>1000 asexual parasites/μL whole blood) or *P. vivax* (>250/μL) will be eligible if they have i) no features of severity,22 ii) not taken a study drug in the previous 28 days, iii) no clinical (including anthropometric) or laboratory evidence of another infection or co-morbidity including malnutrition. Informed consent will be obtained from parents/guardians.

*Clinical/laboratory procedures:* An initial (Day 0) history will be taken and physical examination performed. Blood will be taken for measurement of haemoglobin and glucose. Treatment allocation will be by computer-generated randomized design in blocks of 24 by site:

1. AL (Novartis Pharma, Basel, Switzerland) as artemether 1.7 mg/kg and lumefantrine 10 mg/kg twice-daily for three days,

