2. AP (Pyramax) as artesunate 3 mg/kg and pyronaridine tetraphosphate 9 mg/kg once-daily for three days, and
3. AN (Arco) as artemisinin 20 mg/kg and naphthoquine phosphate 8 mg/kg once-daily for three days (as justified above).

Combinations of full, half- or quarter-tablets will be swallowed whole or crushed lightly before administration. AL-treated subjects will be given tablets or suspension with milk; because there is no such recommendation for AP or AN, pharmacokinetic studies our group will perform during 2009 will determine whether these ACTs should also be given with milk. Only the evening AL doses will be unsupervised, being given at home by parents/guardians. Children vomiting within 30 minutes will be re-treated.

Standardized review including microscopy will be scheduled on Days 1, 2, 3, 7, 14, 28 and 42, with all data, including symptoms, unscheduled clinic visits and non-study treatment, entered on detailed case report forms. Children developing uncomplicated or severe malaria will be given DP at the clinic or intramuscular artemether at the local referral hospital, respectively as per the most recent PNG National Treatment Guidelines.23 All blood films will be re-examined by two skilled microscopists blinded to treatment. Slides discrepant for positivity/negativity, speciation or parasitaemia (>3x difference) will be adjudicated by a senior microscopist. The primary endpoints constitute ACPR under WHO-recommended assessment.24 Early treatment failure (ETF) will be taken as the development of severity or an inadequate parasitological response by Day 3. Any child developing parasitaemia between Days 4 and 42 will be considered late parasitological failure (LPF) or, if febrile, late clinical failure (LCF).

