*Interim analysis:* Although the AN regimen to be used in the trial has been developed using detailed efficacy and safety assessment, a validated assay and conventional pharmacokinetic modelling in PNG children, we will perform an interim analysis after the first 50 children have received this form of treatment. This analysis will be done by the Data and Safety Monitoring Committee ([name] (UPNG), [name] (UWA) and [name] UWA – statistician) who will decide whether the AN arm should be retained for the rest of the trial. The criteria to be used will be i) day 3 parasitaemia positive >25% of children, ii) gametocyte carriage >25% on day 7 and/or iii) >25% attrition rate by day 7.

If AN is withdrawn, children in this arm will be switched to DP (dihydroartemisinin 2.5 mg/kg and piperaquine phosphate 20 mg/kg daily for three days; Sigma Tau, Rome, Italy) given with milk at each dose. DP was one of the arms in our original treatment trial8 and is currently recommended second-line treatment in PNG for uncomplicated malaria in children. However, there has been the suggestion that cure rates might improve if fat were co-administered with this form of ACT to enhance bioavailability,28 as it is with AL. As per the Manufacturer’s instructions, DP was administered with water in the original trial.8 All study procedures will remain the same for children in this group.

*Data analysis:* Statistical analysis will be by *a priori* plan. Per-protocol analyses will include children with complete follow-up or a confirmed treatment failure, and will exclude those treated for malaria without confirmatory microscopy or who defaulted from follow-up despite repeated attempts at contact. These excluded patients will be retained in modified intention-to-treat analyses utilizing:

1. a worst-case approach (ETF assumed for Day 3 exclusions, LPF/LCF otherwise) and
2. a best-case approach (all missing blood films assumed parasite-negative).8

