Kaplan-Meier estimates will be computed for each endpoint by parasite species. Treatments will be compared by log-rank test. Safety and tolerability will be assessed from the incidence of symptoms/signs to Day 7 using Poisson regression (frequent events) or Fisher’s exact test (infrequent events). Blinded interim efficacy analyses and safety assessments will be performed under the auspices of the DSMC and the trial terminated prematurely if one treatment violates the non-inferiority margin or unexpected toxicity emerges. Comprehensive health care cost data will be collected for each patient from Day 0 to Day 42 as is being done currently for the previous trial,8 but indirect costs (e.g. reduced parental/guardian income due to the child’s illness) will also be ascertained in the present trial.

Cox regression using backward-stepwise modelling will be used to determine predictors of treatment failure among age, sex, measures of growth/nutrition, baseline haemoglobin, baseline parasitaemia, Day 7 partner drug concentrations and drug-specific IC50 values. We will utilise population pharmacokinetic modelling using NONMEM (Project Group, University of California San Francisco) and models of *P. falciparum* parasite development based on our animal studies to estimate MIC and derive secondary variables of clinical importance such as the time, in 48-hour parasite life-cycles, above MIC. We have performed host genotyping for red cell traits including thalassemia, South-east Asian ovalocytosis and Gerbich antigen blood group as predictors of response in previous studies and may, if other relevant pharmacogenetic data emerge, extend the proposed analyses to include other polymorphisms.

*Duration/feasibility:* The trial will run from June 2010 to June 2013. We recruited 742 eligible children at Alexishafen and Kunjingini in the East Sepik over 2.3 years in the initial trial,8 and foresee no difficulties in recruiting 870 children to the present study over 3 years. The longer time period for the new study allows for the effect of reduced local transmission when AL is introduced.

**Sub-study 1: Effect of treatment on gametocyte carriage during follow-up** *(Secondary Aim 3)*

*Hypotheses:* i) High field gradient magnetic fractionation (HFGMF) can be used to develop a simple but sensitive field test for gametocyte transmission; ii) AL, AP and AN have similar effects on gametocyte carriage for both *P. falciparum* and *P. vivax* infections.

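### Poisson regression for frequent symptoms to Day 7 is named without a variance estimator or counting unit; its default standard errors would be too large for a per-child yes/no outcome, so robust errors clustered on child should be stated

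*Protocol*

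**What the plan says.** The Data analysis part of the Main Study (Protocol, RESEARCH PLAN) gives safety one sentence: "Safety and tolerability will be assessed from the incidence of symptoms/signs to Day 7 using Poisson regression (frequent events"). For the rarer outcomes that sentence names a different method, "Fisher’s exact test (infrequent events"). It does not say whether the count is of children with a symptom or of symptom reports. It does not say how standard errors are obtained, and it does not define frequent.

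Under Clinical/laboratory procedures, the visit schedule is given as follows: "Standardized review including microscopy will be scheduled on Days 1, 2, 3, 7, 14, 28 and 42". On what is recorded at those visits, the text adds: "with all data, including symptoms, unscheduled clinic visits and non-study treatment, entered on detailed case report forms". Up to Day 7 there are therefore four post-treatment reviews at which one child could report the same symptom.

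Tolerability and safety are named in the primary aim. The endpoint list places them among the other secondary endpoints for each species ("and drug safety including haemoglobin levels"). The protocol also states: "Statistical analysis will be by *a priori* plan". That plan is not at hand.

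**The concern.** A Poisson model takes the variance of the outcome to equal its mean and the observations to be independent. Symptom data to Day 7 need not meet either condition.

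- **One yes/no per child.** Children are independent, but the variance is p(1-p), not p. The default standard error is too large, and the excess grows with p. The protocol reserves this model for frequent events, where the misfit is greatest.
- **Reports summed over reviews.** A child who reports a symptom on one day may well report it on the next. Positive within-child correlation pushes the variance above the mean, and the default standard error usually becomes too small.

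On the first reading, a real excess of symptoms on AP or AN is less likely to be detected. On the second, arms may appear to differ only because symptoms cluster within children.

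**Working it through.** The protocol gives no symptom rate, alpha, power or precision for safety, so there is no figure of its own to reproduce.

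**Inputs**
- Reviews to Day 7: four (Days 1, 2, 3 and 7), from the visit schedule.
- Children per arm: 220 + 60 = 280, adding the two drop-out-inflated group sizes in the sample-size table, which assumes that "there will be equal numbers in each treatment arm". Pooling the species is an assumption.
- Two-sided 5% level: an assumption.
- Incidence p and within-child correlation rho: assumptions, shown as ranges.

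**(a) One yes/no per child**

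Variance/mean = 1-p. The default standard error is too large by 1/sqrt(1-p), and the actual type I error is 2 × [1 - Φ(1.96/sqrt(1-p))].

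| p | SE too large by | Actual type I error |
|---|---|---|
| 0.05 | 2.6% | 4.4% |
| 0.10 | 5.4% | 3.9% |
| 0.20 | 12% | 2.8% |
| 0.30 | 20% | 1.9% |
| 0.40 | 29% | 1.1% |
| 0.50 | 41% | 0.6% |

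For power with n per arm, let d = ln(p2/p1). The default standard error is s_P = sqrt[1/(n·p1) + 1/(n·p2)]. The correct one is s_T = sqrt[(1-p1)/(n·p1) + (1-p2)/(n·p2)]. Power with default errors is about Φ[(d - 1.96·s_P)/s_T]; with correct errors it is about Φ[d/s_T - 1.96].

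Example, 20% v 31%, n = 280: d = 0.438, s_P = 0.171, s_T = 0.149. Default: Φ[(0.438 - 0.336)/0.149] = 75%. Correct: Φ[2.94 - 1.96] = 84%.

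| Comparison (280/arm) | Default | Correct | Loss (points) |
|---|---|---|---|
| 10% v 20% | 87% | 90% | 3 |
| 20% v 31% | 75% | 84% | 8 |
| 40% v 52% | 57% | 81% | 24 |

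Losses are taken before rounding. If the falciparum group is analysed alone (n = 220), the same formulae give 64% v 74% for 20% v 31%.

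**(b) Reports summed over four reviews**

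Variance/mean = (1-p)(1+3·rho), and the actual type I error is 2 × [1 - Φ(1.96/sqrt(variance/mean))]. For p = 0.20 and rho = 0.3: 0.8 × 1.9 = 1.52, and 1.96/1.233 = 1.590, giving 11%.

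| p | rho 0 | rho 0.1 | rho 0.3 | rho 0.5 |
|---|---|---|---|---|
| 0.10 | 3.9% | 7.0% | 13.4% | 19.1% |
| 0.20 | 2.8% | 5.5% | 11.2% | 16.6% |
| 0.30 | 1.9% | 4.0% | 8.9% | 13.8% |

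The two departures cancel where (1-p)(1+3·rho) = 1, that is at rho of about 0.04, 0.08 and 0.14 for p = 0.10, 0.20 and 0.30.

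**After the fix**

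In simulations at 280 per arm with no true difference, a sandwich variance clustered on child gave type I error of 4.2-5.1% for (a) with p from 0.05 to 0.50. For (b) it gave 4.5-5.4% with p from 0.05 to 0.30 and rho from 0 to 0.7.

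**The case against.** The strongest reply is that the protocol names only the regression. Poisson regression with a robust variance fits its words fully, and the variance estimator and counting unit are commonly left to an analysis plan, which the protocol invokes and which is not shown. That stands: their absence is not an error, and the protocol contradicts nothing here. What remains is that the only model statement at hand, applied with its defaults, is poorly matched to the outcomes assigned to it.

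A reader might infer that the protocol prescribes an unadjusted Poisson model whose p-values and intervals are wrong whichever way symptoms are counted. The documents do not support that. No variance estimator is stated. The two counting rules err in opposite directions and only one can apply. For some combinations of p and rho the default is close to correct. Nothing says that repeat reports are summed, and the pairing with Fisher's exact test, which classifies each child once, points to the per-child reading.

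Three further limits stand. The largest power losses arise only at high incidence; at 5-10% the standard error is off by 3-5%. Pooling to 280 per arm is not described, and the endpoint list points to analysis by species. No alpha, margin or stopping rule is tied to this test.

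**Conclusion.** The point holds as a minor improvement, not as an error in the protocol. If default standard errors are used and each child is scored yes/no, the safety comparison is conservative. That direction needs no assumed rate, but the size does: the power loss runs from about 3 points at 10% v 20% to 24 points at 40% v 52%, with 280 per arm and a two-sided 5% level. If reports are summed, type I error at 20% incidence is about 11-17% for rho of 0.3-0.5 and close to nominal at 0.1. The documents supply neither incidence nor correlation, so they cannot show which error applies or how large it is. The point is worth acting on because tolerability and safety belong to the primary aim and the remedy restores nominal error rates under either reading.

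**What to change.** Keep the log-link Poisson model for frequent symptoms and signs, and add wording to this effect in the Data analysis text or the analysis plan:

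- state the counting unit, either each child scored once per symptom to Day 7 or reports counted across the Day 1, 2, 3 and 7 reviews;
- use robust (sandwich) standard errors clustered on child, or log-binomial regression if each child is scored yes/no;
- report AP:AL and AN:AL ratios with 95% confidence intervals.

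The cost is a sentence or two of wording and one option in the analysis code. It needs no new data and no change to the design or sample size.

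### The interim efficacy rule ends the whole trial when one treatment breaches a margin that applies only to the falciparum comparisons, and it does not fix what a breach is

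*Protocol*

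**What the plan says.** Three parts of the Protocol's RESEARCH PLAN (Main Study) bear on this.

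- **Sample sizes.** The falciparum assumption is "PCR-corrected ACPR for AL is 95.2%8 with a non-inferiority margin of 5% for AP and AN". The table gives that study a total of 515, 220 per group with drop-outs, and one-sided alpha 0.05. Vivax has its own row: a superiority comparison with 60 per group and no margin.
- **Interim analysis.** For AN only, "we will perform an interim analysis after the first 50 children have received this form of treatment". The criteria are Day 3 parasitaemia, Day 7 gametocyte carriage and attrition by Day 7. The DSMC are the people "who will decide whether the AN arm should be retained for the rest of the trial". If AN is withdrawn, that arm changes to DP and study procedures continue.
- **Data analysis.** "Blinded interim efficacy analyses and safety assessments will be performed under the auspices of the DSMC", with "the trial terminated prematurely if one treatment violates the non-inferiority margin or unexpected toxicity emerges". This sentence gives no statistic, confidence level, number of looks or look times, and does not mention the AN rule.

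**The concern.** The first problem is the consequence. The trigger belongs to a single treatment, but the action falls on the trial. The trial contains two falciparum non-inferiority comparisons that share AL, and a vivax superiority study sized separately. A shortfall of AP against AL in falciparum malaria says nothing against AN, and it is not a result on the vivax endpoint. Followed literally, the sentence would still leave both of those questions unanswered. The Protocol's Background singles out efficacy against *P. vivax* as of particular interest, and the Interim analysis paragraph shows that the failure of one arm was foreseen.

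The second problem is the trigger. A non-inferiority margin can be said to be violated in at least three senses, and early in a trial these behave very differently. The committee could not apply the sentence predictably, and on two of the three readings it could end a three-year, 870-child trial by chance although all three drugs were equally good.

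**Working it through.** **Consequence: the two rules side by side**

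| | Interim analysis paragraph | Data analysis sentence |
|---|---|---|
| Applies to | AN only | any one treatment |
| Trigger | Day 3 and Day 7 measures, attrition by Day 7 | the non-inferiority margin (defined for Day 42 falciparum response), or unexpected toxicity |
| Timing | after 50 AN children | not stated |
| Action | arm replaced, trial continues | trial terminated |

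Both can be followed, because the triggers differ. What the text does not settle is what happens if AN passes the early screen and later falls short on the margin, or why one arm's failure costs one arm under the first rule and the whole trial under the second.

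**Trigger: how often equal drugs would cause a stop**

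The Protocol states no false-stop probability, so there is no figure of its own to reproduce.

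Inputs from Sample sizes:
- Response 95.2%, taken as true in all three arms; margin 5 points.
- "there will be equal numbers in each treatment arm" and "there will be a 25% attrition rate".
- Evaluable children per arm at the end: 515/3 ≈ 172, or 220 × 0.75 = 165.

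Assumed, because not stated: single looks at 50, 86 (half of 172), 110 (two-thirds of 165) and 165 evaluable falciparum children per arm.

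Let d be the observed AL response minus the new arm's response, with SE = √[(p₁(1−p₁) + p₂(1−p₂))/n]. At the true values with n = 50, SE = √(2 × 0.952 × 0.048/50) = 0.0428, or 4.3 points, which is close to the margin itself. Each arm expects 50 × 0.048 = 2.4 failures. Five points are 2.5 children, so three more failures than AL exceed the margin.

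The three readings of a violation are:
- (a) observed deficit above the margin: d > 0.05;
- (b) non-inferiority not yet shown: d + 1.645·SE ≥ 0.05;
- (c) inferiority beyond the margin shown: d − 1.645·SE > 0.05.

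The chance that AP or AN meets the rule is Σ P(AL = c)·[1 − (1 − q_c)²]. Here c is the number of AL responders and q_c is the exact binomial probability that one new arm meets the rule given c.

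| Evaluable per arm | (a) | (b) | (c) |
|---|---|---|---|
| 50 | 20.4% | 84% | 0.2% |
| 86 | 9.8% | 72% | 0.1% |
| 110 | 7.6% | 66% | 0.04% |
| 165 | 2.8% | 49% | 0.01% |

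A bivariate normal approximation (correlation 0.5 through the shared AL arm) gives 20.0% for (a) at 50 per arm, which agrees. If the true response is 94% or 97% in all arms, (a) at 50 per arm gives 24% or 13%.

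Repeated looks, by simulation of 200,000 trials: reading (a) gives 23% over looks at 50/100/150 per arm, 37% over six looks every 25 to 150, and 11% over 86/172. Reading (c) stays at about 0.6% over the six looks.

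**What reading (c) gives up**

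Take looks at 41/82/124 per arm (quarters of 165) and AL at 95.2%. An arm truly 10 points worse is flagged by the third look in about 47% of trials with a one-sided 95% bound, and in about 20% with a 99% bound. At a true response of 88% the figures are 22% and 6%.

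**The case against.** The strongest reply is that a high false-stop rate is not a property of the text. A reader might infer that equally effective drugs would halt this trial in a fifth of cases or more. That needs reading (a) together with an early look, or reading (b), and the Protocol fixes neither. Reading (c) is at least as natural and makes a false stop rare. The only look at 50 in the document belongs to the AN screen: its 50 are AN children of unspecified species, judged on other measures. This objection stands, and the percentages are conditional.

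A reader might also infer that the two passages contradict each other. They do not, because their triggers and timing differ. Nor does the word blinded mean that the arms are pooled. A pooled look could not reveal which arm breaches a between-arm margin, but the document never says pooled, and analysis by coded arm is a plausible meaning.

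Finally, boundaries and look times commonly sit in an analysis plan or committee charter, and the Protocol refers to an a priori plan that is not shown. Their absence alone is no finding. This does not rescue the consequence, however. The Protocol itself says that the trial ends, and a lower-level document should not have to overturn that sentence.

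**Conclusion.** The point holds in two parts. The firm part needs no arithmetic: the clause attaches a whole-trial consequence to one arm's result on a falciparum-only margin. It would sweep in the other new arm and the vivax study, and it is not reconciled with the arm-level consequence in the Interim analysis paragraph. The second part is that the trigger has no fixed meaning. With all arms at 95.2%, one look at an assumed 50 evaluable children per arm gives a false-stop chance of about 20%, 84% or under 1%, depending on the reading. On the observed-deficit reading it falls to about 10% at 86 and 3% at 165 per arm. These figures rest on assumed look times, Wald limits at the one-sided 95% level and equal true responses. They show how much hangs on the wording. They do not estimate what the committee would actually do.

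**What to change.** Rewrite the efficacy half of the sentence and leave the toxicity half alone:

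1. Make the clause act on the affected arm's falciparum comparison with AL. State that AL, the other new arm and the vivax study continue.
2. State that a violation means a confidence limit for the difference from AL lying wholly beyond −5 points. Say that neither a point estimate beyond the margin nor non-inferiority not yet shown is enough. The confidence level and looks can be left to the DSMC.
3. Say that the interim comparison uses coded arms.
4. Reconcile the Interim analysis and Data analysis text on whether one failing arm ends that arm or the trial, and on how the AN rule and the margin rule relate.

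This costs one paragraph in the Protocol and matching text for the DSMC, with no change to sample size or treatment. The real price is slower detection: at the looks shown above, an arm 10 points worse is missed in about half of trials with a 95% bound and in about four-fifths with a 99% bound. The level should be chosen with those figures in view.

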**Secondary aims:**

1. To determine, using sensitive magnetic methods, the effect of each ACT regimen on gametocyte carriage during the six-week trial follow-up period.

2. To determine the duration of post-treatment prophylaxis using passive case detection of symptomatic malaria infections presenting over a period of six months after trial follow-up.

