*Background:* We have developed HFGMF gametocyte detection based on the unique metabolism of iron in the parasite and commercially available magnetic separation columns (Miltenyi Biotech). The method relies on magnetic concentration of gametocytes which are then identified more readily on a smear (see Figure 2) than by conventional expert microscopy.29 It has a similar sensitivity to reverse transcriptase PCR (RTPCR, data submitted; see Table), but is much quicker and cheaper.

[figure not shown]

| Gametocyte density | HFGMF (time taken) | Thick film (time taken) | RT-PCR |
| --- | --- | --- | --- |
| 2,970/µL | Positive (<1 minute) | Positive (<1 minute) | Positive |
| 297/µL | Positive (<1 minute) | Positive (7 minutes) | Positive |
| 29.7/µL | Positive (<1 minute) | Positive (28 minutes) | Positive |
| 2.97/µL | Positive (9 minutes) | Negative | Positive |
| 0.297/µL | Negative | Negative | Negative  HFGMF detection at 3/μL |

The method could be used to quantify the gametocidal efficacy of ACT assuming that transmission is unlikely at a gametocyte density <3/μL,30 a threshold detectable by HFGMF but not microscopy.

*Methods:* We will take a small additional sample of mixed capillary blood at each follow-up visit from 25 children in each treatment and species arm on which HFGMF and RTPCR will be performed as well as conventional microscopy. The differences in gametocyte carriage by detection method over time between treatment arms will be determined using General Linear Modelling for repeated measures, applying square-root transformation to allow for the effect of zero values on the density distribution at each time point and identifying important non-treatment-related covariates.

**Sub-study 2: Duration of post-treatment prophylaxis using passive case detection of symptomatic malaria during the six months after trial follow-up** *(Secondary Aim 5)*

*Hypothesis:* The duration of post-treatment prophylaxis for AL, AP and AN is a function of the t½*e* of the non-artemisinin partner drug alone.

*Background:* For some long half-life drugs such as piperaquine, urinary excretion studies suggest unexpected persistence of low plasma concentrations.31 In addition, the antimalarial activity of atovaquone in sera is sustained beyond that predicted by its pharmacokinetic properties.32 Whether these sorts of effects are of clinical importance in ACT-treated patients is unknown, even for DP.

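### Sub-study 1 analyses gametocyte carriage, a yes/no outcome, with a normal-error repeated-measures model of square-root density, which does not resolve the zeros, does not suit RT-PCR and may use only complete series

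*Protocol*

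**What the plan says.** Secondary aim 1 of the Protocol is to determine "the effect of each ACT regimen on gametocyte carriage during the six-week trial follow-up period". Sub-study 1, Methods, takes extra capillary blood at each follow-up visit from "25 children in each treatment and species arm on which HFGMF and RTPCR will be performed", alongside conventional microscopy. What is compared is "The differences in gametocyte carriage by detection method over time between treatment arms". The model is "General Linear Modelling for repeated measures, applying square-root transformation to allow for the effect of zero values" on the density distribution at each time point.

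The Background of the same sub-study supposes that transmission is unlikely below 3 gametocytes/µL, "a threshold detectable by HFGMF but not microscopy". Its table gives RT-PCR results only as positive or negative.

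Four other places in the Main Study bear on the point:

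- Clinical/laboratory procedures: review is "scheduled on Days 1, 2, 3, 7, 14, 28 and 42", which is seven follow-up visits. A finger-prick smear is also taken at baseline.
- Clinical/laboratory procedures: "Children developing uncomplicated or severe malaria will be given DP at the clinic" or a different drug at hospital, so some children receive another antimalarial during the gametocyte series.
- Sample sizes: "there will be a 25% attrition rate". Day 42 vivax ACPR is taken as 30.3% for AL and at least double that for AP and AN.
- Data analysis: worst-case and best-case rules are given for treatment failure and missing blood films. No rule is given for gametocyte densities in incomplete series or after re-treatment.

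**The concern.** The aim and the Methods both name carriage, but the model is one of mean transformed density. These are different quantities, and a difference in mean square-root density cannot be read back as a difference in the proportion of children carrying gametocytes. The mismatch is sharpest for RT-PCR, where the protocol describes no density to transform.

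The transformation is meant to deal with zeros, but the square root of zero is zero. However many children are gametocyte-free at a visit, the same share sits at zero afterwards, beside a skewed tail of positives. With 25 per arm, normal-theory errors cannot be relied on.

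The usual multivariate form of a repeated-measures General Linear Model also needs a value at every visit. Where attrition is expected and failure differs by arm, children with complete series may be few and may be selected differently in each arm.

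At stake is the between-arm answer to Secondary aim 1. The primary endpoints do not depend on it.

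**Working it through.** The 25 per arm comes without an effect size, alpha or power, so there is no calculation to reproduce. Three checks follow.

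**1. Does the square root change the zeros?** √0 = 0, so the share of zeros is the same before and after. Illustration with assumed inputs (positives lognormal, median 30/µL, log-SD 1.5):

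| Carriage | Zeros after square root | Skewness after square root |
| --- | --- | --- |
| 50% | 50% | 3.2 |
| 25% | 75% | 4.7 |
| 10% | 90% | 7.1 |
| 5% | 95% | 10.2 |

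The protocol forecasts no carriage rates. The nearest figure is the interim criterion for AN (Main Study, Interim analysis), which uses carriage above 25% on Day 7. An arm at that limit would have 75% zeros.

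**2. What does this do to a comparison of two arms of 25?** I simulated one visit with the same assumed densities, identical among carriers in both arms, and 20,000 runs at two-sided 0.05. A t-test on square-root density was compared with an uncorrected chi-square test of positive versus negative.

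| Carriage in the two arms | t-test, square-root density | Chi-square, yes/no |
| --- | --- | --- |
| 25% v 25% (null) | 4.0% | 5.4% |
| 10% v 10% (null) | 2.1% | 4.8% |
| 25% v 60% | 45% | 76% |
| 10% v 40% | 51% | 73% |
| 5% v 30% | 50% | 71% |

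Sensitivity:

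- At 50% carriage in both arms, the t-test is near nominal (4.7%) and the chi-square slightly liberal (6.5%).
- For the three alternatives, t-test power is 57% to 61% with log-SD 1.0 and 34% to 41% with log-SD 2.0.
- Fisher's exact test, itself conservative, has 65%, 59% and 55% power for the three alternatives at log-SD 1.5. It still beats the t-test there, but is roughly level with it at log-SD 1.0.

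**3. How many complete series?** Inputs from the Protocol: 25 per arm, attrition 25%, vivax ACPR 30.3% (AL) and at least 2 × 30.3% = 60.6% (AP, AN). Attrition is assumed independent of failure.

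- Only attrition removes children: 25 × 0.75 = 18.75, about 19 in any arm.
- Only failures leave, AL vivax: 25 × 0.303 = 7.6, about 8.
- Both, AL vivax: 25 × 0.75 × 0.303 = 5.7, about 6.
- Both, AP or AN vivax: 25 × 0.75 × 0.606 = 11.4, about 11. This is a minimum, because 60.6% is a floor.
- Both, AL falciparum: 25 × 0.75 × 0.952 = 17.9. This is at most about 18, because 95.2% is PCR-corrected and does not count re-infections.

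If failures instead stay in the series, some later values follow re-treatment. Upper bounds are 18.75 × (1 − 0.303) = 13.1 AL children and 18.75 × (1 − 0.606) = 7.4 AP or AN children. The true numbers are lower if parasitaemia without fever is not re-treated.

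**The case against.** **The plan does not state complete-case deletion.** This stands. The phrase could cover a mixed model using all available visits, and nothing says visits stop at failure. A reader might infer that the plan leaves about 6 of 25 AL vivax children in the analysis. The documents do not support that as a fact: 6 is the low end of a range of about 6 to 19. It also treats every failure as ending the series, whereas the protocol separates parasitaemia alone from febrile failure and does not say that every child with afebrile parasitaemia gets DP.

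**A square root is defined at zero.** This stands. It would be wrong to say that the model cannot be run with zeros. It can be run, but the transformation does not achieve its stated purpose.

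**Re-treatment does not destroy randomisation.** A reader might infer that DP given during follow-up leaves no randomised comparison. That is untrue if all visits are kept and analysed by allocated arm: the result is then the effect of a policy that includes re-treatment. Only dropping children or visits according to outcome introduces selection.

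**Yes/no gametocyte outcomes are covered elsewhere.** Appearance of gametocytes within 42 days is a secondary endpoint for both species, with Kaplan-Meier and log-rank analyses. This helps, but it is not the comparison by detection method and visit that Sub-study 1 sets out to make.

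**This belongs in the SAP.** The handling of missing visits does, and its absence here is not counted as an error. The model, the transformation and its rationale, however, are fixed in the Protocol.

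**The alternative has limits.** A logistic mixed model can separate or fail to converge with 25 per arm and few late positives, and ordinary GEE needs data missing completely at random. If treatment also lowers density among carriers, a density analysis carries information that a yes/no analysis loses. These points shape the fix without rescuing the stated model.

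**Conclusion.** The concern holds in a limited form. Three parts need no numerical assumption: carriage is not what the model estimates, RT-PCR as tabulated offers no density to transform, and the square root leaves the share of zeros unchanged.

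The loss of precision is illustrative. At 10% to 25% carriage the test rejected a true null in 2% to 4% of runs. Power was 45% to 51% against 71% to 76% for an uncorrected yes/no test. This rests on assumed carriage rates, a lognormal spread, equal density among carriers and a single visit. The gap narrows with less spread or with an exact test.

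The loss of children is conditional. If only complete series are used, about 19 of 25 per arm remain under attrition alone. If every failure also ends the series, as few as about 6 in AL vivax remain, against at least about 11 in AP or AN vivax. The protocol does not say which applies.

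This should be changed, but it is a weakness in a secondary sub-study; the primary endpoints are unaffected.

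**What to change.** - Make carriage the outcome: positive or negative by each detection method and, for HFGMF, also at the 3/µL threshold. Fit a mixed-effects logistic model with visit, arm and arm-by-visit terms, using all available visits from every sampled child.
- State in advance a penalised fit, or pooling of late visits, for use if positives are sparse.
- Adjust for the Day 0 gametocyte result from the smear already collected. HFGMF and RT-PCR are described only at follow-up visits, so baseline adjustment by those methods should not be assumed.
- Analyse by allocated arm with all visits, including those after re-treatment. Add a sensitivity analysis censored at re-treatment, noting that this censoring depends on outcome and may differ by arm.
- Analyse density, where measured, with a two-part or negative-binomial mixed model.

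The cost is a change of wording and slightly more complex modelling. No new samples, visits or children are needed. The trial is open-label, so the change is best made before gametocyte results are seen by arm.
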